##### Secondary efficacy analyses

Secondary efficacy analyses will be conducted in the full analysis set. Proportions of patients achieving remission or other binary responses will be compared between groups using Pearson’s Chi-squared tests. Changes in Gaussian-distributed continuous interval variables over time will be compared between groups using mixed between-within subjects ANOVA; if the data do not meet the assumptions of the test, approaches such as rank transformation will be used. Time to event analyses will be conducted using log-rank tests. Analyses will be repeated in the per protocol set.

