#### Secondary objectives

To assess the change in MRI synovitis between baseline and 48 weeks following very early ETN or MTX-TT regimen +/- delayed ETN.To evaluate other clinical efficacy endpoints at weeks 12, 24, 48 and 96 including:✓ Disease activity score-44 joint (DAS44) remission (DAS44 < 1.6), simplified disease activity index (SDAI), clinical disease activity index (CDAI), European League Against Rheumatism (EULAR) response criteria, American College of Rheumatology (ACR) response criteria.✓ Cumulative steroid dose.To evaluate patient-reported outcomes at weeks 12, 24, 48 and 96 including:✓ Physical function, assessed by the Health Assessment Questionnaire (HAQ), including normalisation of HAQ.✓ Quality of life scores assessed by RA Quality of Life (RA-QoL) and Euro QoL Five Dimensions (EQ-5D) questionnaires.✓ Work instability, assessed by RA Work Instability Score (RA-WIS) questionnaire.To evaluate imaging predictors of remission and sustained remission using:✓ High-resolution ultrasound (HRUS) at weeks 0, 12, 24 and 48 measuring grey scale (GS), PD and presence or absence of erosions.✓ Magnetic Resonance Imaging (MRI) at weeks 0, 12, 24 and 96 measuring synovitis and erosion scores.To evaluate other radiographic outcomes including:✓ Joint damage assessed by modified Sharp score of X-rays of hands and feet at weeks 48 and 96.

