#### Imaging assessments

*MRI (high field gadolinium enhanced)* of the dominant hand and wrist (or alternative hand in the instance of greater clinical evidence of synovitis at baseline) will be performed at baseline, weeks 12, 24, 48 and 96. The dominant hand will be scanned unless the alternative hand has clinical evidence of greater synovitis at baseline. This study will use MRI to assess erosions, synovitis and bone marrow oedema using the accepted standard of RA magnetic resonance imaging score (RAMRIS), as well as direct synovial volume measurement and sensitive dynamic contrast enhanced magnetic resonance imaging (DCE-MRI) for quantification of synovitis and bone marrow oedema. Failure of MRI acquisition after baseline will not constitute a protocol violation and will not necessitate withdrawal from the study.

RAMRIS scoring system: scoring of erosions, synovitis and bone marrow oedema, using the validated outcome measures in RA clinical trials (OMERACT) system, will be performed by 2 independent, experienced scorers. The RAMRIS scoring system is a standardised, reliable, validated scoring system for synovitis, erosion and oedema. It has been successfully used to demonstrate response to treatment, including bDMARD [35]. Direct volume measurement of synovitis by manual segmentation will be performed. This will allow quantification of low volumes of synovitis not differentiated by RAMRIS scoring.

This will be followed by dynamic contrast enhanced (DCE)-MRI. Early enhancement rates measured from DCE-MRI depend strongly on synovial vascularity and capillary permeability and are therefore potentially better markers of inflammatory activity than simple volume measurements. DCE-MRI measurement of bone marrow oedema will also be performed.

A blinded assessor will perform *HRUS (Philips HDI 5000)* of the same hand and wrist as chosen for MRI at baseline, weeks 12, 24 and 48. If the target joint for synovial biopsy is at another site, the target joint will also be scanned. Images will be assessed for synovitis, using semi-quantitative scores of GS and PD and for presence or absence of erosions.

Plain radiographs of bilateral hands (carpal, MCP and PIP joints) will be performed at baseline, 12 and 24 months after the start of study medication to assess structural damage. Radiographs will be scored as per the modified Genant-modified Sharp scoring system [36].

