### Statistical considerations

#### Sample size

Clinical remission (DAS28 remission) forms the basis of the primary outcome. The COMET study, reported remission rates in patients with very early RA (less than 4 months since diagnosis) treated with both ETN and MTX or MTX monotherapy of 70 % versus 35 % respectively. In patients with disease duration of less than 2 years but greater than 4 months, treatment with ETN and MTX was associated with 48 % remission rate. In the COMET study patients in the very early RA group were recruited within 4 months of RA diagnosis, using ACR 1987 criteria. In contrast, VEDERA will recruit patients within 12 months of symptom onset. Whilst all patients will meet RA criteria at the point of recruitment, ACR/EULAR 2010 criteria are being used, which identify patients at an earlier stage of the disease course than the 1987 criteria, and patients can potentially be recruited concurrently with diagnosis. It is likely that patients recruited to VEDERA will be at a similar stage in their disease course to the patients in the very early RA group in COMET, potentially an even earlier stage.

To account for the possibility that the interval between the treatment groups may not be as large as that seen in COMET a 30 % difference has been used as a basis for the sample size calculation. Assuming therefore that patients in treatment arm 1 are likely to achieve up to 70 % remission, and treatment arm 2 approximately 40 % remission; for 80 % power at the 5 % significance level and allowing for a 10 % dropout rate, at least 49 patients per arm will be required. Increasing this to 60 per arm would allow for a subgroup analysis of treatment arm 2 patients that proceed to require delayed ETN and MTX to be compared with treatment arm 1 and indeed those in arm 2 that stay on conventional therapy. This is an exploratory analysis; we estimate that 50 % of treatment arm 2 patients will require delayed ETN and MTX. With roughly 30 patients in each subgroup of treatment arm 2 we will obtain sufficiently accurate estimates of remission rates.

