#### Analyses

Descriptive summary statistics will be provided for all variables at baseline and at each visit at which the variable is assessed. For continuous variables the following information will be provided: number of patients (N), mean, standard deviation, minimum, median, maximum and 25 % and 75 % quartiles. For categorical data frequency (absolute and relative) distributions will be provided. Differences between groups will be summarized according to data type and 95 % confidence intervals around these estimates will be constructed.

All inferential analyses will be conducted using two-tailed tests at the 5 % level of significance. The Holm correction (modified Bonferroni) will be employed on a family-wise basis to control for multiple comparisons of secondary outcomes.

Complete details of statistical analyses and methods, including data handling conventions, will be contained in a separate statistical analysis plan which will be finalized before the database is locked.

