##### Other planned analyses

Immunological, gene expression and histological parameters will be compared between the two treatment arms using the same approaches listed for the secondary analyses with appropriate bioinformatics as indicated; subgroup analyses will repeat the between-arm comparison, split by remission status (achieved/not achieved).

Clinical, imaging, synovial and immunological factors associated with the odds of early and sustained remission will be investigated using univariable and multivariable binary logistic regression models.

RAMRIS score is considered a secondary efficacy outcome and will be analysed accordingly. For the remaining exploratory imaging and biological endpoints, descriptive summaries will be provided for all variables but inferential tests will not be performed.

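### Continuous secondary outcomes, including MRI synovitis, are compared as changes by ANOVA without baseline as a covariate: a valid test, but less precise than a baseline-adjusted one

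*Protocol article*

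**What the plan says.** The section Secondary efficacy analyses fixes one method for continuous outcomes: "Changes in Gaussian-distributed continuous interval variables over time will be compared between groups using mixed between-within subjects ANOVA". The fallback names no baseline term either: "if the data do not meet the assumptions of the test, approaches such as rank transformation will be used".

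MRI synovitis comes under this method. The first-listed secondary objective is "To assess the change in MRI synovitis between baseline and 48 weeks", and Other planned analyses adds: "RAMRIS score is considered a secondary efficacy outcome and will be analysed accordingly". Under Imaging assessments the scans "will be performed at baseline, weeks 12, 24, 48 and 96", so a baseline value is planned for each patient. HAQ and RAQoL fall under the same sentence, as do SDAI and CDAI if they are analysed as scores.

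The Analyses section states: "All inferential analyses will be conducted using two-tailed tests at the 5 % level of significance". It applies a Holm correction to the secondary outcomes and leaves full detail to a separate SAP, which is not shown. The article gives no SD, effect size or baseline-to-follow-up correlation for any continuous outcome.

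**The concern.** In a between-within ANOVA that includes baseline as one of the time points, the treatment effect on change is the group-by-time term. With baseline and one later visit, this term is the same test as a t-test on change scores. The baseline value is subtracted with a coefficient fixed at 1, whatever the data say about how well baseline predicts follow-up. ANCOVA estimates that coefficient, and in large samples it is never less precise.

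What is at stake is power and the width of confidence intervals for the continuous secondary outcomes, in a trial of 120 patients that was sized on a binary primary outcome.

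**Working it through.** **The plan's own figure.** There is none for a continuous outcome. The only sample-size statement concerns DAS28 remission, 70 % against 40 %, "for 80 % power at the 5 % significance level and allowing for a 10 % dropout rate", giving at least 49 per arm. A pooled two-proportion calculation gives 42 per arm, and 42/0.9 = 46.7, so 47 after dropout. This is within two patients of 49 and has no bearing on the present point.

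**Inputs.**
- From the article: 60 per arm, 10 % dropout, two-sided 5 %. Patients with data: 60 × 0.9 = 54 per arm.
- Assumed: r = 0.3 to 0.7, equal SDs at baseline and follow-up, and a true difference of 0.5 SD (for the power illustration only).

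**Step 1, variance.** In units of SD², per patient:
- change score: 2(1-r)
- ANCOVA: 1-r²
- ratio of ANCOVA to change: (1-r²)/[2(1-r)] = (1+r)/2
- share of the sample lost by using change: 1-(1+r)/2 = (1-r)/2

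**Step 2, power.** The approximation is Φ(0.5/√(2v/54) - 1.96), with v the variance from step 1. At r = 0.3 the change score has √(2 × 1.4/54) = 0.228, so 0.5/0.228 - 1.96 = 0.24 and power is 59 %. ANCOVA has √(2 × 0.91/54) = 0.184, so 0.5/0.184 - 1.96 = 0.76 and power is 78 %.

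| r | v, change | v, ANCOVA | sample lost | of 120 | power, change | power, ANCOVA |
|---|---|---|---|---|---|---|
| 0.3 | 1.40 | 0.91 | 35 % | 42 | 59 % | 78 % |
| 0.5 | 1.00 | 0.75 | 25 % | 30 | 74 % | 85 % |
| 0.7 | 0.60 | 0.51 | 15 % | 18 | 92 % | 95 % |

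These figures are at an unadjusted 5 % level. The Holm correction would lower both power columns.

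**Step 3, simulation with baseline and one follow-up** (normal data, 54 per arm, 8,000 runs per setting). The group-by-time test and the change-score t-test gave identical power: 58.6 %, 73.8 % and 91.3 % at r = 0.3, 0.5 and 0.7. ANCOVA gave 76.3 %, 84.8 % and 94.4 %. With no true effect, every rejection rate lay between 4.7 % and 5.1 %.

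**Step 4, several visits.** With baseline and three follow-ups, equal correlation between all visits and a constant 0.5 SD effect after baseline, the omnibus group-by-time test had power of 59 %, 76 % and 94.5 %. ANCOVA at the last visit alone had 77 %, 84 % and 95 %. The gap remains at low r and almost closes at 0.7.

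**Step 5, unequal SDs.** With SDs s0 at baseline and s1 at follow-up, the change-score variance is s0² + s1² - 2r·s0·s1 and the ANCOVA variance is s1²(1-r²). The difference is (s0 - r·s1)², which is never negative. The loss grows if s1 falls somewhat below s0 and shrinks if s1 is somewhat larger.

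**Step 6, chance imbalance in the realised sample.** A change score carries -(1-r) times the baseline difference into the estimate. With 60 per arm the standard error of that difference is √(2/60) = 0.18 SD (0.19 SD with 54). An imbalance of one standard error shifts the estimate by 0.7 × 0.18 = 0.13 SD at r = 0.3, 0.5 × 0.18 = 0.09 SD at r = 0.5, and 0.3 × 0.18 = 0.05 SD at r = 0.7. This variation is already contained in the variance in step 1.

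**The case against.** The best defence is that the planned method is valid. Under randomisation the change comparison is unbiased and holds its type I error, so this is a matter of efficiency, on secondary outcomes only. That stands, and it limits the weight of the point.

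A second defence is that covariates are commonly left to the SAP, to which the article refers. This stands only in part. The SAP may well add a baseline term, but the article does not leave the method open. It names one, and an SAP that follows it inherits the loss.

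Third, the calculation assumes normal data, and nothing shows that RAMRIS synovitis will be so distributed. If the rank fallback is used, the figures above are a guide only. The fallback as worded adds no baseline adjustment either.

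Four stronger readings are tempting, and the document does not support them:
- **A fixed fraction lost.** A reader might infer that a quarter to a third of the sample is wasted. That needs r between 0.33 and 0.50, and the article gives no r. At r = 0.8 the loss is 10 %.
- **Bias from the choice of hand.** The imaging section says: "The dominant hand will be scanned unless the alternative hand has clinical evidence of greater synovitis at baseline". This may induce regression to the mean, but the rule uses baseline findings and is the same in both arms, so it does not bias the comparison.
- **Unstratified randomisation.** The article mentions only 1:1 block randomisation. Silence in a condensed article does not show that there were no stratification factors.
- **Imbalance as a second harm.** Chance imbalance does shift the realised estimate, but it is a component of the same precision loss and must not be counted twice.

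**Conclusion.** The point holds as one of precision. The named analysis of continuous secondary outcomes omits the baseline covariate and is, in large samples, never more precise than one that includes it. For the week-48 contrast the share of the sample lost is (1-r)/2, about 35 % to 15 % for an assumed r of 0.3 to 0.7 with equal SDs. In power terms the cost is substantial at r = 0.3 (19 points for a 0.5 SD effect) and slight at r = 0.7 (about 3 points). For the omnibus test over several visits the size depends on the visit pattern and the correlations.

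Nothing here makes the test invalid, inflates the type I error or touches the primary outcome. It is worth changing because the gain costs almost nothing.

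**What to change.** Replace the between-within ANOVA by a baseline-adjusted analysis:
- For outcomes with several follow-ups, use a linear mixed model for repeated measures of the post-baseline values, with baseline value, arm, visit, arm-by-visit and baseline-by-visit as terms.
- For outcomes with a single follow-up of interest, use ANCOVA with the baseline value as covariate.

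Report the adjusted difference between arms with its 95 % confidence interval at each named visit, and state week 48 as the contrast for MRI synovitis.

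The cost is the rewording of one sentence, carried into the SAP before the database is locked. The baseline values are already collected, and no extra patients or visits are needed.

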##### Other planned analyses

Immunological, gene expression and histological parameters will be compared between the two treatment arms using the same approaches listed for the secondary analyses with appropriate bioinformatics as indicated; subgroup analyses will repeat the between-arm comparison, split by remission status (achieved/not achieved).

Clinical, imaging, synovial and immunological factors associated with the odds of early and sustained remission will be investigated using univariable and multivariable binary logistic regression models.

RAMRIS score is considered a secondary efficacy outcome and will be analysed accordingly. For the remaining exploratory imaging and biological endpoints, descriptive summaries will be provided for all variables but inferential tests will not be performed.

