#### Exploratory objectives

To investigate immunological abnormalities and cellular/molecular predictors of response to the two therapeutic strategies using:✓ Blood, sampled at baseline and weeks 12, 24, 36, 48 and 96.✓ Synovial tissue (optional), biopsied from a target joint at baseline and 24 weeks; at 48 weeks for treatment arm 2 who have switched to ETN and at time of flare.

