## Discussion

This pragmatic, randomised phase IV, open-label study is comparing first line ETN and MTX combination therapy with a TT regimen starting with MTX monotherapy regimen with sDMARD escalation followed by ETN and MTX at week 24 if the treatment target of remission (or LDA with physician impression of remission) is not achieved.

The fundamental objective of this study is to determine whether TNFi instituted as first-line therapy in early RA confers better outcomes (including depth of remission and exploratory parameters indicating normalisation of immune system aberration) compared to a conventional TT therapeutic approach with delayed TNFi if required. The VEDERA study will contribute to the existing evidence [37, 38] and in addition addresses the question of whether quality of response to TNFi following MTX-failure differs from that achieved with first-line use, prior to MTX exposure. The accurate imaging aligned with the clinical assessments will also ensure correct categorisation of patient response, to address the weaknesses of clinical composite measures for assessing remission [39].

Although the planned sample size (*n*=120) is relatively small, the study is adequately powered to detect a clinically meaningful difference in remission rate, based on existing published data. Secondary outcomes are expected to be correlated with the primary outcome and we therefore anticipate the effect size to be similar for these variables, which are considered supportive of the primary hypothesis. For exploratory endpoints the focus will be purely descriptive; the sample size has been inflated to help ensure that planned subgroup analyses of patients receiving delayed ETN will include sufficient patients, based on rules of thumb for pilot studies.

One of the secondary objectives of the study is remission maintenance and sustainability after ETN withdrawal. There is increasing published data regarding this [40], and while this study does not primarily seek to investigate drug tapering following remission, it will provide additional insights. Finally, the biosamples collected will allow investigation of the pathobiology of disease, mechanisms of drug action and predictors of response and remission in order to enable more effective tailoring of therapy in clinical practice.

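### Exploratory biology is to be tested between arms and again within remission strata, against the Discussion's descriptive-only statement; the remission-split comparisons are not randomised

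*Protocol article*

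**What the plan says.** The biological work is listed under Exploratory objectives: "To investigate immunological abnormalities and cellular/molecular predictors of response to the two therapeutic strategies".

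Other planned analyses then gives it an inferential treatment: "Immunological, gene expression and histological parameters will be compared between the two treatment arms using the same approaches listed for the secondary analyses". The approaches borrowed are those of Secondary efficacy analyses: chi-squared tests, mixed ANOVA or rank transformation, and log-rank tests. The same sentence continues: "subgroup analyses will repeat the between-arm comparison, split by remission status (achieved/not achieved".

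The last paragraph of that section says of the remaining exploratory imaging and biological endpoints that "descriptive summaries will be provided for all variables but inferential tests will not be performed". The Discussion makes no exception: "For exploratory endpoints the focus will be purely descriptive".

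On error rates, the Analyses section says "All inferential analyses will be conducted using two-tailed tests at the 5 % level of significance", and "The Holm correction (modified Bonferroni) will be employed on a family-wise basis to control for multiple comparisons of secondary outcomes".

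**The concern.** There are two separate problems.

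1. **Two instructions.** One section of the article plans tests of exploratory biology, while the Discussion describes exploratory endpoints as descriptive. An analyst could follow either and claim to have followed the protocol.
2. **Conditioning on an outcome.** Remission is what the trial expects treatment to change. If arm 1 brings more patients into remission, its remitters include patients with a poorer outlook who would not have remitted in arm 2, and the non-remitters it leaves are a harder group. In both strata the arms then differ in prognosis. Any marker linked to prognosis can differ between arms there, even if treatment does nothing to it.

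Immunological normalisation is part of the stated main aim. A difference between arms among remitters could therefore be read as a difference in the biological quality of remission when it reflects selection.

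**Working it through.** **Inputs from the documents.** Remission 70 % in arm 1 and 40 % in arm 2, 80 % power, 5 % significance, 10 % dropout, at least 49 per arm, raised to 60 (Sample size). Two-sided tests at 5 % (Analyses). The sentence on the remission split names no visit; I take remission as the week 48 primary outcome.

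**The plan's own figure.** The disputed section states none. The sample size from the same rates is n = [1.96 × √(2 × 0.55 × 0.45) + 0.842 × √(0.7 × 0.3 + 0.4 × 0.6)]² / 0.30² = 42 per arm, and 42/0.9 = 47 with dropout. That is within 2 of the stated 49, so the 70 % and 40 % are taken as the working rates.

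**Size of the strata (60 per arm).** Remitters: 60 × 0.70 = 42 v 60 × 0.40 = 24. Non-remitters: 18 v 36. The smallest difference detectable with 80 % power, (1.96 + 0.842) × √(1/n₁ + 1/n₂), is 0.51 SD overall, 0.72 SD in remitters and 0.81 SD in non-remitters.

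**Selection within strata.** Let the marker be U ~ N(0,1), the same in both arms, with logit P(remission) = a + bU. The intercept a is set separately by arm to give 70 % and 40 %. The mean of U by arm and stratum gives the spurious difference. The values of b are assumptions.

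| b (log-odds per SD) | Remitters, arm 1 − arm 2 (SD) | Non-remitters, arm 1 − arm 2 (SD) |
|---|---|---|
| 0.2 | −0.06 | −0.06 |
| 0.5 | −0.14 | −0.14 |
| 1.0 | −0.25 | −0.26 |
| 1.5 | −0.31 | −0.34 |

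For example, at b = 0.5 the mean of U among remitters is 0.143 in arm 1 and 0.284 in arm 2, a difference of −0.14.

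**Effect on the test.** A simulation used 54 per arm (60 × 0.9), 8,000 runs per scenario, and a marker with no treatment effect that shares a prognostic factor with remission. The overall comparison rejected in about 5 % of runs in every scenario. Within remitters / non-remitters, rejection was 7.1 % / 6.6 % at an assumed marker–remission latent correlation of 0.25, 14.8 % / 13.6 % at 0.49, and 31.4 % / 30.9 % at 0.72.

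**Multiplicity, if no correction applied.** The number of markers is not stated; take 20. Tested overall and in two strata, that is 20 × 3 = 60 tests, and 60 × 0.05 = 3 expected false positives whatever the correlation. If all 60 tests were independent, the chance of at least one would be 1 − 0.95⁶⁰ = 0.954. They are not, because each overall test contains the same patients as its two strata. A simulation with 60 per arm and markers unrelated to remission or treatment gives:

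| Correlation between markers | Chance of at least one false positive |
|---|---|
| 0 | about 91–92 % |
| 0.3 | about 84–86 % |
| 0.5 | about 73–74 % |
| 0.7 | about 55–57 % |

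**The case against.** Several stronger readings are tempting, and the document does not support them.

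- **That Other planned analyses contradicts itself.** Its last paragraph bars tests only for the remaining exploratory imaging and biological endpoints. That can be read as an ordinary carve-out after the three named classes, and it can cover imaging measures such as synovial volume and dynamic contrast-enhanced MRI. The tension that stands is with the Discussion, and even there it is with one summarising sentence about focus.
- **That every between-arm test of the biology is confounded.** It is not. The overall comparison is by randomised arm, and the simulation shows its error rate at about 5 %. A separate limit is that synovial biopsy is optional.
- **That the tests have no error control.** The stated scope of Holm is "to control for multiple comparisons of secondary outcomes", which does not exclude a correction elsewhere. The plan to borrow the secondary approaches with suitable bioinformatics leaves room for one, and full methods are deferred to an analysis plan that is not shown. Silence here is not a defect.
- **That at least one false positive is 95 % certain or more.** That figure needs 60 independent tests and is not a lower bound.

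It is also fair that the split serves a stated aim. Whether remission looks the same biologically under both strategies can only be examined among remitters, and the protocol makes no causal claim for it. This is a good reason to keep the summaries. It does not restore randomisation, so it does not support an arm-by-arm significance test inside the strata.

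**Conclusion.** The point holds in two parts. The testing planned in Other planned analyses and the descriptive stance in the Discussion disagree and must be reconciled. The arm comparisons within remission status condition on an outcome of treatment, so their p-values do not test a treatment effect on the marker.

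The selection difference is about 0.06 to 0.34 SD. It rests on the plan's 70 % v 40 % and on assumed log-odds of 0.2 to 1.5 per SD, and is negligible for markers unrelated to remission. It matters most for markers that predict remission, which the trial sets out to find.

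The multiplicity figures (about 3 expected false positives, roughly a 55–92 % chance of at least one) are conditional on 20 markers and on no correction being set. They show the scale and do not establish an omission. The weight is modest: the biology is exploratory, and primary and secondary inference are untouched.

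**What to change.** 1. Make Other planned analyses and the Discussion agree on whether the immunological, gene expression and histological parameters are tested or only described.
2. Present remission-split results as descriptive estimates with 95 % confidence intervals, labelled as non-randomised, with no between-arm significance test inside the strata.
3. If overall between-arm tests are kept, control the false discovery rate across all markers tested and say so in the analysis plan.

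The cost is wording, which the analysis plan can carry because it is to be finalised before database lock. The small downside is fewer nominal p-values in the exploratory reports.

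### Predictor models for remission do not provide for treatment arm, so an on-treatment marker that only reflects etanercept exposure may often look associated with remission

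*Protocol article*

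**What the plan says.** The model sentence is in Other planned analyses: "factors associated with the odds of early and sustained remission will be investigated using univariable and multivariable binary logistic regression models". The factors are of four kinds: immunological, synovial, imaging and clinical. The sentence does not mention treatment arm, or the visit at which a factor is measured.

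Two objectives feed these models:

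- Secondary objectives: "To evaluate imaging predictors of remission and sustained remission using" ultrasound at weeks 0, 12, 24 and 48, and MRI at weeks 0, 12, 24 and 96.
- Exploratory objectives: "To investigate immunological abnormalities and cellular/molecular predictors of response to the two therapeutic strategies", with "Blood, sampled at baseline and weeks 12, 24, 36, 48 and 96" and optional synovial biopsies at baseline and later.

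Both lists run beyond baseline. The second objective asks about response to two strategies, not about remission in general.

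The same section also plans between-arm comparisons of immunological, gene-expression and histological parameters, repeated within patients who did and did not reach remission. For the remaining exploratory imaging and biological endpoints, "descriptive summaries will be provided for all variables but inferential tests will not be performed". The Analyses section leaves complete details to a separate analysis plan.

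**The concern.** A univariable model of a marker holds that marker and nothing else. If it is fitted to all randomised patients, it cannot separate the marker from the treatment.

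Up to week 24 etanercept is given in arm 1 only, so a marker that the drug moves is also a marker of arm. The trial is designed on the expectation that arm 1 remits more often. Arm then links marker and remission even where the marker says nothing about which patient on a given treatment will remit.

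A second problem does not depend on confounding. One odds ratio per marker describes remission averaged over both strategies. The objective concerns "cellular/molecular predictors of response to the two therapeutic strategies", which needs the association in each arm and a comparison of the two.

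At stake is the content of a stated secondary objective (imaging predictors) and a stated exploratory one (cellular and molecular predictors). Markers of drug exposure could be reported as predictors, and the by-strategy question could go unanswered although the randomised arms supply the data for it.

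**Working it through.** **Inputs from the protocol article.** Remission 70 % in arm 1 and 40 % in arm 2 (Sample size); 120 patients, 1:1, so 60 per arm (Study design); two-sided 5 % (Analyses). The protocol states no sample size or error rate for the predictor models.

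**Input assumed.** The shift *s* of the marker in arm 1, in within-arm SDs. The documents give none, so a range is used.

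**The plan's own figure.** n per arm = [1.96·√(2·0.55·0.45) + 0.842·√(0.21 + 0.24)]² / 0.30² = (1.379 + 0.565)² / 0.09 ≈ 42. Then 42/0.9 = 46.7, so 47, against the stated 49. This is close enough to take 70 % and 40 % as the planning rates.

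**Limiting case: marker identical to arm.** Remission is 42/60 v 24/60.

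- OR = (42/18)/(24/36) = 3.5
- SE(log OR) = √(1/42 + 1/18 + 1/24 + 1/36) = 0.386
- 95 % CI = exp(1.253 ± 1.96·0.386) = 1.64 to 7.45
- chi-squared = 120·(42·36 − 18·24)²/(60·60·66·54) = 10.9, p about 0.001

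This is simply the planned treatment effect, carried by a marker with no predictive value inside either arm.

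**Partial shift.** Let the marker be normal with SD 1 in each arm, shifted by *s* in arm 1 and unrelated to remission given arm. Across both arms its correlation with remission is

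r = (s·Δ/4) / √[(1 + s²/4)·p̄(1 − p̄)],

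with Δ the remission difference and p̄ the mean rate. The test statistic is centred near λ = r·√120, and the chance of p < 0.05 is about Φ(λ − 1.96) + Φ(−λ − 1.96).

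For s = 1 at 70 % v 40 %: r = 0.075/√(1.25·0.2475) = 0.135, λ = 1.48, probability 31 %.

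The simulated columns come from logistic models with Wald tests, 60 per arm, in runs of 1,500 to 4,000 trials. They show the range over runs.

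| Remission | s (SD) | Approximation, no arm | Simulated, no arm | Simulated, arm included |
|---|---|---|---|---|
| 70 v 40 % | 0.5 | 13 % | 12–14 % | 4–5 % |
| 70 v 40 % | 1.0 | 31 % | 30–31 % | 4–5 % |
| 70 v 40 % | 1.5 | 51 % | 49–52 % | 4–5 % |
| 70 v 50 % | 0.5 | 8 % | 7–8 % | 4–5 % |
| 70 v 50 % | 1.0 | 17 % | 15–17 % | 4–5 % |
| 70 v 50 % | 1.5 | 27 % | 26–27 % | 4–5 % |
| 50 v 50 % | 0.5 to 1.5 | 5 % | 4–5 % | 4–5 % |

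At 54 per arm (10 % loss), 70 % v 40 % and shifts of 0.5 and 1 SD, the rates without arm are 10 % and 28 %.

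**After week 24.** Arm 2 patients not in remission at week 24 move to etanercept; the protocol expects about half of arm 2 to do so. From then on, exposure within arm 2 depends on earlier remission status. An arm term alone no longer removes the link between a drug-driven marker and remission, so the calculation above covers markers read up to week 24 only.

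**The case against.** Several points on the other side stand.

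- The text does not say that the arms are combined. Models run separately in each arm would remove the confounding, and the phrase about two strategies is compatible with that. A reader might infer that a pooled analysis is fixed. It is only the apparent reading: the paragraph before names the two arms and the logistic sentence does not.
- Multivariable models are planned in the same sentence and can contain arm. Nothing excludes arm from them, and nothing requires it.
- A reader might infer that exposure markers will be declared predictors. The documents do not support that. They contain no declaration rule, they speak of factors associated with remission, and the Discussion calls the focus for exploratory endpoints purely descriptive.
- Baseline markers are independent of arm on average because of randomisation. The confounding does not apply to them.
- The shifts are assumed, and 70 % and 40 % are planning rates for week 48 remission, not for the early and sustained remission that these models address.
- Covariate lists and measurement times for exploratory models are commonly left to the analysis plan.

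These points limit the claim but do not remove it. The protocol itself fixes the univariable form, and over all patients that form cannot adjust for arm. The clause that withholds inferential tests covers the remaining exploratory endpoints, and imaging predictors are a secondary objective. The planned between-arm comparison split by remission status would help a reader recognise a drug effect, but it does not estimate the association of marker with remission within an arm.

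**Conclusion.** The concern holds in a limited form. The planned predictor models do not provide for randomised arm, while the objectives list on-treatment measurements among the predictors.

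The size rests on three assumptions: models over all patients, a remission difference as planned, and a marker shift of 0.5 to 1.5 SD by etanercept before week 24 with no within-arm association. Under these, the chance of a nominally significant result is roughly 13 % to 50 %, against about 5 % with arm in the model. It falls to 7 % to 27 % at 70 % v 50 %, and to the nominal level if remission does not differ.

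For baseline markers the limitation is a different one: a single odds ratio cannot separate a predictor of response to one strategy from a general prognostic factor.

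The primary analysis does not depend on these models, so severity is low.

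**What to change.** Amend the logistic regression sentence in Other planned analyses, and carry the change into the analysis plan:

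1. Include or stratify on randomised arm in every predictor model, including those with a single marker.
2. Require each marker to be measured before the remission that it is meant to predict. For markers after week 24, use by-arm or landmark analysis.
3. Report the marker odds ratio within each arm with its interval, plus an arm-by-marker interaction labelled exploratory.

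This needs no new data or visits, only revised wording and one or two extra terms per model. The price is wider intervals, low precision for the interaction at 60 per arm, and fewer nominally significant markers.
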